### Matching Criteria

Donor urine output over the last 24 hours before retrieval, cold ischemic time (CIT), and the recipients Charlson comorbidity index [20] have been selected as matching criteria. Matching will be performed using a propensity score [21].

### Kidney Transplantation

Kidney grafts will be implanted heterotopically to the iliac fossa, as per our institutional protocol. The renal vein is anastomosed first, end-to-side to the external iliac vein, followed by renal artery anastomosis to the external iliac artery in the same fashion. After reperfusion of the kidney, the ureter is implanted into the bladder, according to Lich-Gregoir, and the uretero-cystostomy is stented with a 6-French double-J stent.

### Sample Collection and Storage

Ischemia reperfusion injury will be assessed using kidney tissue samples taken upon arrival of the organ (before HOPE) and at the end of implantation after reperfusion, but before closure of the abdomen, to evaluate the extent of IRI (Figure 3). In total, two biopsies using BARD MONOPTY Disposable Core Biopsy Instrument (Bard Biopsy Systems Inc, Tempe, Arizona) will be harvested from the ECD kidney allograft and used for translational research. During machine perfusion, perfusate samples will be collected every 20 minutes. Blood samples are taken as part of the daily routine during the perioperative and postoperative course of kidney transplant (Figure 3). Blood parameters of kidney function (ie, creatinine, urea, estimated glomerular filtration rate [eGFR]) will be monitored. An additional 20 mL of blood will be drawn on postoperative days 1, 2, 3 and 7 and will be used for translational research (Figure 3). All kidney tissue, serum, and perfusate will be directly snap-frozen in liquid nitrogen (−80°C) and stored for 6 months after completion of the trial. To assess the subcellular mechanisms of HOPE in the clinical setting, various parameters, including markers of kidney injury (creatinine and neutrophil gelatinase-associated lipocalin (NGAL) in plasma samples), tissue ATP concentration, inflammatory mediators (eg, tumor necrosis factor alpha, interleukin-6, macrophage migration inhibitory factor, interleukin-10, monocyte chemoattractant protein-1), and biomarkers of oxidative damage (eg, 8-hydroxy-2'-deoxyguanosine), will be analyzed [11,12].

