**Methods:**

A total of 15 kidney allografts with defined inclusion/exclusion criteria will be submitted to two hours of HOPE via the renal artery before implantation, and are going to be compared to a case-matched group of 30 patients (1:2 matching) who had kidneys transplanted after conventional cold storage. Primary (posttransplant dialysis within 7 days) and secondary (postoperative complications, early graft function, duration of hospital and intensive care unit stay, and six-month graft survival) endpoints will be analyzed within a six-month follow-up period. The extent of ischemia-reperfusion injury will be assessed using kidney tissue, perfusate, and serum samples taken during the perioperative phase of kidney transplantation

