### Immunosuppression and Postoperative Care

All patients will be treated according to our institutional protocol. Aside from HOPE for the donor kidneys, all procedures, including peri- and intraoperative management, are conducted in accordance with standard surgical kidney transplant management. The applied immunosuppressive regimen is based on intraoperative induction therapy with intravenous methylprednisolone and either basiliximab or thymoglobulin followed by corresponding oral doses of prednisolone, tacrolimus, and mycophenolate mofetil.

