### Study Endpoints

The primary endpoint is DGF, which is defined as the need for dialysis in the first 7-days posttransplantation. The secondary endpoints of the study include: (1) duration of DGF (defined as the period between kidney transplant and last dialysis in days) and functional DGF (defined as <10% fall in serum creatinine for 3 consecutive days in the first week posttransplantation); (2) creatinine reduction ratio day 2 ([creatinine day 1−creatinine day 2]/creatinine day 1) and Creatinine reduction ratio day 5 ([pretransplant creatinine−creatinine day 5]/pretransplant creatinine); (3) incidence of postoperative complications, as assessed by the Clavien-Dindo complication score and the comprehensive complication index [22]; (4) duration of intensive care and hospital stay; (5) recipient and graft survival after six months; (6) renal function (assessed by serum creatinine and eGFR) at one-, three- and six-months post-transplant; and (7) basic and translational research, which involves assessing biomarkers from routinely harvested kidney tissue and serum following implantation to obtain information on kidney injury, extent of oxidative damage, redox- and energetic homeostasis of the implanted donor kidney.

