### Ischemia-Reperfusion Injury and Inflammation

IRI is an inevitable event in organ transplantation. Reduction of oxygen delivery because of blood flow interruption leads to anaerobic metabolism and the production of oxygen-free radicals and oxidative stress as a respiratory burst at the onset of reperfusion. IRI plays a key role in DGF and primary graft nonfunction following kidney transplantation, depending on initial organ quality [8,9,24,25]. To detect the effects of HOPE on IRI, the kidney tissue, blood, and perfusate samples obtained in this study will be used to quantify several innovative parameters of inflammation (eg, interleukins, tumor necrosis factor-alpha), kidney injury (Cytatin-C, NGAL, etc) energy- (ATP levels) [11,26], and redox-threshold (Hemoxygenase-1, Malondialdehyde) [12,27]. Luminometry, Spectrophotometry, Luminex-assay, Enzyme-linked immunosorbent assay (ELISA), Reverse transcriptase polymerase chain reaction (RT-PCR) and Western blot will be used for these analyses. Proteomics and metabolomics analysis will be performed on kidney tissue samples to potentially identify early mediators of HOPE-mediated organ protection.

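### Research blood is listed only from postoperative day 1, so plasma NGAL and the other research markers measured in blood have no pre-transplant value to be read against

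*Protocol article*

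**What the plan says.** The protocol article, Sample Collection and Storage, fixes the research blood: "An additional 20 mL of blood will be drawn on postoperative days 1, 2, 3 and 7 and will be used for translational research". The same section adds that "Blood samples are taken as part of the daily routine during the perioperative and postoperative course of kidney transplant", but the parameters it names for monitoring there are those of kidney function (creatinine, urea, eGFR). Study Endpoints, item 7, describes the biomarker endpoint as "assessing biomarkers from routinely harvested kidney tissue and serum following implantation".

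Tissue is treated differently: "Ischemia reperfusion injury will be assessed using kidney tissue samples taken upon arrival of the organ (before HOPE) and at the end of implantation", the second sample being taken after reperfusion. Perfusate is collected every 20 minutes during perfusion. Creatinine also has a pre-transplant value, because the day 5 reduction ratio uses one.

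The Ischemia-Reperfusion Injury and Inflammation section says that tissue, blood and perfusate will be used to detect the effect of HOPE on the injury, and describes "oxidative stress as a respiratory burst at the onset of reperfusion". Immunosuppression and Postoperative Care gives every patient "intraoperative induction therapy with intravenous methylprednisolone and either basiliximab or thymoglobulin". The caption of Figure 3 lists an admission visit (Visit 2) before the visits on days 1, 2, 3 and 7.

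**The concern.** The blood markers are meant to help gauge the extent of reperfusion injury and the effect of HOPE on it. Every listed research draw falls after reperfusion, after surgery and after induction. All recipients have end-stage renal disease, so their marker levels before transplantation cannot be assumed to be normal or alike. The article reports no such levels, so how far they differ is unknown. Without a pre-transplant value, a day 1 level carries whatever the recipient brought to the operation, and that part cannot be removed.

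The control group does not fill the gap. It is historical, and the article describes no research serum for it. A between-group comparison of these markers may not exist, which makes the recipient's own starting level more valuable. The article presents its translational work as a focus and a strength of the study, and a pre-transplant sample that was not taken cannot be recovered later.

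**Working it through.** The article gives no sample size or power figure for the biomarkers, so there is nothing to reproduce. The check sets the sampling times side by side, then illustrates what a baseline is worth.

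**1. Reference value before the injury, by measurement**

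| Measurement | Before reperfusion | After reperfusion |
|---|---|---|
| Kidney tissue | On arrival, before HOPE | End of implantation |
| Perfusate | Every 20 minutes during HOPE | Not applicable |
| Creatinine | Pre-transplant value (day 5 ratio) | Routine blood |
| Plasma NGAL and other research markers in blood | None listed | Days 1, 2, 3 and 7 |

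Only the last row lacks a reference. Of the markers in that row, the article ties NGAL to plasma. The inflammatory and oxidative markers are listed without a matrix, or for tissue, blood and perfusate together, so the point covers them only so far as they are measured in blood.

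**2. What can and cannot be calculated**

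- Change from pre-transplant: unavailable for 15 of 15 HOPE patients on the stated schedule.
- Change between days 1 and 7: available.

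**3. Value of a baseline (illustration)**

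Let r be the correlation between the pre-transplant and the later level. The documents do not give it; 0.4 to 0.7 is assumed. Equal variances at the two times are also assumed, and the degree of freedom spent on the adjustment is ignored.

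- Residual variance after baseline adjustment, as a fraction of the raw variance: 1 − r².
- Equivalent number of patients: 15/(1 − r²).
- Variance of raw change, as a multiple of the raw variance: 2(1 − r).

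| r | 1 − r² | Cut in variance | 15/(1 − r²) | 2(1 − r) |
|---|---|---|---|---|
| 0.4 | 0.84 | 16% | 17.9 | 1.2 |
| 0.5 | 0.75 | 25% | 20.0 | 1.0 |
| 0.7 | 0.51 | 49% of raw removed | 29.4 | 0.6 |

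Note on the last row: 1 − 0.51 = 0.49, so the residual variance is 51% of the raw variance and the cut is 49%. The range of cuts is therefore 16% to 49%.

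Adjustment never does worse than the raw level in this approximation. Raw change does worse whenever r is below 0.5: at r = 0.4 its variance is 20% higher.

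**4. The same on the scale of a group comparison**

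Suppose marker data existed for 15 HOPE patients and 30 controls, with two-sided alpha 0.05 and 80% power. The detectable difference is (1.96 + 0.84) × √(1/15 + 1/30) = 0.89 SD without a baseline. Multiplying by √(1 − r²) gives 0.77 SD at r = 0.5 and 0.63 SD at r = 0.7. The gain is useful, but a comparison of postoperative levels alone is not worthless.

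**The case against.** **Absence is not proved.** Figure 3, cited for the blood schedule, is not shown, its caption includes an admission visit, and the Abstract says the injury "will be assessed using kidney tissue, perfusate, and serum samples taken during the perioperative phase of kidney transplantation". An article also condenses a fuller protocol. This stands as a caution. But the text gives an explicit list of days and a post-implantation endpoint, and a general word covering three kinds of sample does not override them.

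**A reader might infer that blood markers cannot show reperfusion injury at all, or that no within-patient change can be computed.** The documents do not support either. Day 1 to 7 levels can be described and related to delayed graft function, and change over those days is calculable. Creatinine has its baseline. The paired biopsies bracket reperfusion, and perfusate adds to them.

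**An admission sample does not isolate reperfusion.** This stands in full. Induction, surgery and the start of graft filtration all lie between admission and day 1. A baseline removes differences that recipients had beforehand. It does not separate those influences from reperfusion or from HOPE, which would need comparably treated controls with samples.

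**The precision gain is speculative.** The correlation is assumed, and the equivalent patient numbers apply to comparisons between patients adjusted for baseline, not to raw change.

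**The remedy trades one time point for another** and leaves patients on two schedules, since enrollment was already under way. That is a real but small cost.

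**Conclusion.** The point holds in a limited form. As written, plasma NGAL and any other research markers measured in blood have no pre-transplant value, so change from the recipient's own starting level is unavailable for all 15 HOPE patients. With historical controls and no research serum described for them, day 1 to 7 levels cannot be cleanly attributed to reperfusion injury or to HOPE.

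The defect concerns one kind of sample within the last-listed secondary endpoint of a pilot study. It does not touch the primary endpoint, creatinine, tissue or perfusate. The size of the precision loss depends entirely on the assumed correlation. The conclusion also assumes that neither Figure 3 nor the full protocol provides an admission research sample.

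**What to change.** - Take one 20 mL research sample at Visit 2 with the routine pre-operative blood, before induction. If it replaces, for example, the day 3 draw, the total stays at 4 × 20 = 80 mL.
- Analyse the blood markers adjusted for that baseline, not as raw change alone.
- Record the induction agent for each patient, and report the blood markers as descriptive.
- If an admission research sample already exists in Figure 3 or the full protocol, reconcile Sample Collection and Storage and Study Endpoints with it.

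The cost is a small amendment to the sampling schedule and the loss of one postoperative time point. Patients already enrolled will have no baseline and should be shown separately in any baseline-adjusted result.

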**Figure 3 figure3:**
[figure not shown]
Interventions and study visits. Numbers represent the single study visit: Visit 1: screening, enrollment; Visit 2: admission; Visits 3, 4, and 5: postoperative days 1, 2, and 3; Visit 6: seventh postoperative day; Visit 7: discharge; Visit 8: 6 months follow-up; final visit. HOPE: hypothermic oxygenated machine perfusion.

### Immunosuppression and Postoperative Care

All patients will be treated according to our institutional protocol. Aside from HOPE for the donor kidneys, all procedures, including peri- and intraoperative management, are conducted in accordance with standard surgical kidney transplant management. The applied immunosuppressive regimen is based on intraoperative induction therapy with intravenous methylprednisolone and either basiliximab or thymoglobulin followed by corresponding oral doses of prednisolone, tacrolimus, and mycophenolate mofetil.

### Study Endpoints

The primary endpoint is DGF, which is defined as the need for dialysis in the first 7-days posttransplantation. The secondary endpoints of the study include: (1) duration of DGF (defined as the period between kidney transplant and last dialysis in days) and functional DGF (defined as <10% fall in serum creatinine for 3 consecutive days in the first week posttransplantation); (2) creatinine reduction ratio day 2 ([creatinine day 1−creatinine day 2]/creatinine day 1) and Creatinine reduction ratio day 5 ([pretransplant creatinine−creatinine day 5]/pretransplant creatinine); (3) incidence of postoperative complications, as assessed by the Clavien-Dindo complication score and the comprehensive complication index [22]; (4) duration of intensive care and hospital stay; (5) recipient and graft survival after six months; (6) renal function (assessed by serum creatinine and eGFR) at one-, three- and six-months post-transplant; and (7) basic and translational research, which involves assessing biomarkers from routinely harvested kidney tissue and serum following implantation to obtain information on kidney injury, extent of oxidative damage, redox- and energetic homeostasis of the implanted donor kidney.

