## Methods

### Study Type and Eligibility

The present trial is an investigator-initiated pilot study on the effects of HOPE on ECD-allografts in donated after brain death kidney transplants. Figure 2 summarizes the trial design.

Patients older than 18 years of age, suffering from end-stage renal disease (ESRD), listed for kidney transplant, and receiving ECD organs at the Department of Surgery and Transplantation, University Hospital Rheinisch-Westfälische Technische Hochschule (RWTH) Aachen, Aachen, Germany, are eligible for the study. Informed consent was obtained from all subjects participating in the trial by a qualified member of the study team. Inclusion and exclusion criteria are listed in Textbox 1.

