**Figure 2 figure2:**
[figure not shown]
Study flow chart. ECD: extended criteria donor; HOPE: hypothermic oxygenated machine perfusion; DGF: delayed graft function; GFR: glomerular filtration rate.

Study inclusion and exclusion criteria.
*Inclusion Criteria:*
Signed informed consent18 years or olderSuffering from ESRD (end-stage renal disease)Listed for kidney transplantReceiving ECD (extended criteria donor)-allografts
*Exclusion criteria:*
Recipients of living donor kidney transplantsPrevious solid organ transplantationCombined procedures (eg, kidney-liver transplantation)Participation in other kidney-related trialsThe subject received an investigational drug within 30 days prior to inclusionThe subject is unwilling or unable to follow the procedures outlined in the protocolThe subject is mentally or legally incapacitatedNon-German or non-English speakersFamily members of the investigators or employees of the participating departmentThe subject suffers from uncontrolled bacterial or viral infection

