### Hypothermic Oxygenated Machine Perfusion Versus Historic Cold Storage Group

Primary and secondary outcomes of patients transplanted with the HOPE-treated kidneys will be compared to a case-matched group of 30 patients (1:2 matching) transplanted with ECD organs after conventional cold storage, using identical surgical techniques and perioperative treatment at the Department of Surgery and Transplantation, University Hospital RWTH Aachen. The present trial comprises two groups, a perfusion (Group 1, HOPE) and a control conventional cold storage group (Group 2, Historic). Patients on the waiting list for kidney transplant with proven written consent will be recruited. HOPE will be applied to the allograft in the operating room after regular organ procurement, transport, and back-table preparation (Figure 1).

We adapted a protocol based on clinical studies with nonoxygenated hypothermic machine perfusion, and on preclinical experience with HOPE [11,18,19]. HOPE will be applied through the renal artery for at least two hours, with a perfusion pressure of 25 mmHg and a perfusion rate of 50-200ml/min using 1 L of recirculated perfusate at 0-4°C. The perfusate will be oxygenated using medical grade oxygen (O^2^), with a partial pressure of oxygen (pO^2^) of 60-80 kilopascals (kPa), by an oxygenator included as a disposable part of the setup. Perfusion parameters registered by the device will be stored automatically and evaluated for possible patterns. Immediately prior to perfusion, grafts will be flushed with perfusate solution to wash out the residual histidine-tryptophan-ketoglutarate (HTK) solution. Storage, management, and use of the medical products will be carried out according to the manufacturer’s guidelines.

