### Study Population

To the best of our knowledge, aside from a sole case of HOPE-treated dual kidney transplant reported recently, no experience of HOPE in human donation after brain death kidney transplant has been published yet [23]. In the present pilot study, 15 patients (N=15) will be treated with HOPE to gain first prospective clinical knowledge. HOPE-treated patients will be compared to a case matched group of 30 patients (N=30).

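### The primary endpoint is dialysis-based DGF, but pre-transplant dialysis dependence is neither an eligibility criterion nor a matching variable, so recipients not yet on dialysis would dilute or bias the comparison

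*Protocol article*

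**What the plan says.** *Study Endpoints* sets the primary outcome: "The primary endpoint is DGF, which is defined as the need for dialysis in the first 7-days posttransplantation". The definition does not refer to whether the recipient was on dialysis before transplantation. Duration of DGF, a secondary endpoint, is counted to the last dialysis and so rests on the same event. *Safety Considerations* applies a chi-squared test to the DGF rate once 10 patients have received HOPE, and ends the trial if the rate is significantly higher than in the matched cold-storage group.

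*Study Type and Eligibility* admits adults "suffering from end-stage renal disease (ESRD), listed for kidney transplant, and receiving ECD organs". The article does not define end-stage renal disease in terms of dialysis, and no entry in the exclusion list concerns dialysis status.

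The comparator is a "case-matched group of 30 patients (1:2 matching) transplanted with ECD organs after conventional cold storage". *Matching Criteria* names three variables, combined in a propensity score: "Donor urine output over the last 24 hours before retrieval, cold ischemic time (CIT), and the recipients Charlson comorbidity index". Only the last describes the recipient, and none records dialysis status or residual native kidney function.

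Two kinds of secondary endpoint do not depend on dialysis: "functional DGF (defined as <10% fall in serum creatinine for 3 consecutive days in the first week posttransplantation"), and creatinine reduction ratios on days 2 and 5.

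**The concern.** Whether a recipient is dialysed in the first week depends on the graft and also on how much native function remains. A recipient not yet on dialysis may get through a week of poor graft function on native kidneys, where a dialysis-dependent recipient could not. The chance of registering as DGF is therefore lower for a reason unrelated to HOPE.

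In a randomised trial this would be balanced on average. Here one group is prospective and the other historical, and matching is the only stated protection against prognostic imbalance. It does not cover the recipient characteristic most directly tied to the endpoint.

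The groups are small. One patient is 1/15 = 6.7 points of the HOPE rate, 1/30 = 3.3 points of the control rate, and 1/10 = 10 points of the HOPE rate at the interim look. An imbalance of a few patients could suggest a benefit or a harm that is not there. At the interim look, more such recipients among controls would push towards a false stop, and more under HOPE would mask a true excess of DGF.

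**Working it through.** **Inputs from the document.** 15 HOPE patients, 30 controls, significance at P<.05. It gives no expected DGF rate, effect size, power or share of recipients not on dialysis, so there is no figure to reproduce. Everything else below is an assumption made to show scale.

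**Model.** Let p be the DGF risk in dialysis-dependent recipients, f the share of a group not on dialysis, and r their DGF risk relative to dialysis-dependent recipients. Then

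observed DGF = p × [(1 − f) + f × r].

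r = 0 is the extreme in which they are never dialysed in week 1; r = 0.25 is a milder assumption.

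**1. Unequal shares, no HOPE effect.** With 3/15 under HOPE (f = 0.20) and 0/30 in controls, at p = 40%:

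- r = 0: HOPE 0.40 × 0.80 = 32%, controls 40%; spurious benefit 8 points.
- r = 0.25: HOPE 0.40 × (0.80 + 0.05) = 34%, controls 40%; spurious benefit 6 points.

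Other splits and base rates, in points:

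| Not on dialysis, HOPE vs controls | r | p = 30% | p = 40% | p = 50% |
|---|---|---|---|---|
| 3/15 vs 0/30 | 0 | 6 benefit | 8 benefit | 10 benefit |
| 3/15 vs 0/30 | 0.25 | 4.5 benefit | 6 benefit | 7.5 benefit |
| 2/15 vs 1/30 | 0 | 3 benefit | 4 benefit | 5 benefit |
| 0/15 vs 3/30 | 0 | 3 harm | 4 harm | 5 harm |
| 0/15 vs 3/30 | 0.25 | 2.25 harm | 3 harm | 3.75 harm |

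**2. Equal shares, true effect 40% vs 20%.** The 20-point difference is multiplied by (1 − f) + f × r:

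- f = 10%: 20 × 0.90 = 18 points (r = 0), or 20 × 0.925 = 18.5 points (r = 0.25).
- f = 20%: 20 × 0.80 = 16 points (r = 0), or 20 × 0.85 = 17 points (r = 0.25).

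Exact power of the two-sided uncorrected chi-squared test at 15 vs 30 is 0.270 at f = 0. At f = 20% it is 0.211 (r = 0) or 0.226 (r = 0.25).

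**3. What restriction does to power.** The 0.270 applies only if all 15 and 30 are dialysis-dependent. If 20% of each group is dropped and not replaced, 12 vs 24 remain, and the same exact calculation at 20% vs 40% gives 0.206. Dropping patients therefore does not recover power. It makes the groups comparable and leaves the difference undiluted.

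**4. Size against sampling error.** At 40% in both groups the standard error of the difference is √[0.40 × 0.60 × (1/15 + 1/30)] = √0.024 = 15.5 points. The spurious 6 to 8 points is about 0.4 to 0.5 standard errors.

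**5. How often chance alone would do this.** If both groups have the same underlying share and 3 of the 45 are not on dialysis, the probability that all 3 fall in the HOPE group is C(15,3)/C(45,3) = 455/14,190 = 0.03. An imbalance that large would more plausibly come from a systematic difference between the prospective and historical cohorts, which the document neither shows nor rules out.

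**The case against.** A reader might infer that recipients not yet on dialysis count as successes whatever the graft does, or that the endpoint cannot be observed in them. The document does not support this. The definition has no condition on prior status, so such a recipient who needs dialysis in week 1 is an event like any other. Their risk is lowered, not fixed at zero, and the r = 0 results above are an upper bound.

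A reader might also assume that such recipients are in the trial. Nothing shows this. Recipients must have end-stage renal disease and be listed, living-donor recipients are excluded, and the *Introduction* reports about 8000 patients waiting in Germany against 2005 postmortem transplants in 2018. That context makes a large share less likely, though it does not exclude one.

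Poor function without dialysis is partly captured by functional DGF and the creatinine ratios. These are secondary, however, and change neither the primary endpoint nor the interim rule.

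The trial is a pilot, in which "15 patients (N=15) will be treated with HOPE to gain first prospective clinical knowledge", and the *Discussion* acknowledges non-randomisation and historical matching. The shifts are small against sampling error, and power is low with or without a change. This limits the weight of the point, but a general caveat about matching does not supply the missing variable.

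Finally, an article leaves detail to the full protocol. A precise definition of end-stage renal disease or a sensitivity analysis could well be there. But eligibility, the primary endpoint and the matching variables are set out here as chosen, and the *Discussion* defends the matching set as carefully selected to cover donor and recipient factors. The choice can be assessed as stated.

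**Conclusion.** The point holds in a limited form. A dialysis-based primary endpoint and stopping rule are compared between non-randomised groups, and no stated criterion makes the groups comparable on pre-transplant dialysis dependence. Recipients not yet on dialysis would dilute the difference if equally represented and bias it if not. Under the assumptions of 40% DGF in dialysis-dependent recipients, no HOPE effect and a 3/15 versus 0/30 split, the spurious benefit is 6 points at r = 0.25 and 8 points at r = 0. Other splits give smaller shifts, or harm instead of benefit.

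These figures rest on assumed rates, shares and relative risks. If no recipient in either group was transplanted before dialysis, the effect is nil. The change is worth making because it is cheap and removes a plausible false signal, not because the document shows that the comparison is already distorted.

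**What to change.** - Record dialysis status at transplantation for every HOPE patient and every candidate control.
- Draw controls matched exactly on that status, in addition to the propensity score, or only from dialysis-dependent recipients.
- Specify that the DGF, DGF-duration and interim DGF comparisons are made in recipients on maintenance dialysis at transplantation, in both groups. Keep any others for the remaining secondary endpoints.
- Report how many in each group were not on dialysis.

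This suits a trial already enrolling better than a new inclusion criterion, which would change the recruited population part-way through.

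The cost is one routine chart item, one constraint on control selection and one sentence defining the analysis population. With exact 1:2 matching, each HOPE recipient not on dialysis leaves the primary comparison together with two controls, so the ratio is kept but the sample shrinks. If there are none, nothing is lost.

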### Data Collection and Statistics

Patients will be given consent forms while in our outpatient clinic. Data will be obtained using study specific CRFs completed by the members of the study team. Subjects will be informed about data protection, including pseudonymization. Encoded data will only be provided to authorized persons (ie, authorized study staff, authorities, institutional review board). The study will be prematurely terminated for any individual subject in case of study-related complications or if the subject withdraws informed consent. Parametric and nonparametric tests will be done according to the normality of the data distribution. Two-way analysis of variance will be used for the time-course analysis of laboratory parameters. The log-rank test will be used for comparisons between Kaplan-Meier curves of six-month graft survival. Statistical significance will be defined as *P*<.05.

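### The day-2 and day-5 creatinine reduction ratios carry no rule for dialysed patients, so as printed a fall caused by dialysis counts as graft function

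*Protocol article*

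**What the plan says.** All the definitions stand in the Study Endpoints section of the protocol article. The primary endpoint reads: "The primary endpoint is DGF, which is defined as the need for dialysis in the first 7-days posttransplantation". Secondary endpoint (2) consists of two ratios, "creatinine reduction ratio day 2 ([creatinine day 1−creatinine day 2]/creatinine day 1" and "Creatinine reduction ratio day 5 ([pretransplant creatinine−creatinine day 5]/pretransplant creatinine". Secondary endpoint (1) includes "functional DGF (defined as <10% fall in serum creatinine for 3 consecutive days in the first week posttransplantation". None of the three creatinine-based definitions mentions dialysis.

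The Data Collection and Statistics section gives general test choices and adds nothing on values measured after dialysis. The comparison is between 15 HOPE patients and a "case-matched group of 30 patients (1:2 matching) transplanted with ECD organs after conventional cold storage".

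**The concern.** Dialysis removes creatinine. A patient with a failing graft who is dialysed between the two samples shows a fall that the formula cannot tell apart from recovery of the graft. Both intervals (day 1 to day 2, and pretransplant to day 5) lie inside the 7-day window of the primary endpoint, so the patients whose ratio can be altered in this way are patients who meet that endpoint.

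The arm with more DGF has more altered values. If HOPE lowers DGF, that is the cold-storage arm, and the ratio comparison is pulled against HOPE. If HOPE raised DGF, the pull would be in its favour. Either way, an endpoint meant to describe early graft function could disagree with the primary endpoint for a mechanical reason.

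Functional DGF has the same gap. A dialysis-induced fall can interrupt the run of three days, so that a patient on dialysis is classed as free of functional DGF.

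**Working it through.** The article gives no DGF rate, expected ratio, standard deviation or dialysis timing, so there is no stated figure to reproduce. From the document come the formulas, the 7-day window and the group sizes (15, and 15 × 2 = 30). Every other input below is an assumption.

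**Model.** Let p be the DGF rate in an arm, m_f the mean ratio of a functioning graft, m_n the mean ratio of a failing graft without dialysis, f the share of DGF patients dialysed between the two samples, and r the fraction of creatinine removed.

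- Ratio of a dialysed failing graft: m_d = 1 − (1 − m_n)(1 − r)
- Arm mean: (1 − p)·m_f + p·[f·m_d + (1 − f)·m_n]
- With m_n = 0, m_d = r, and the difference HOPE minus control is (p_control − p_HOPE)·(m_f − f·r)

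**Day 2, with p = 0.40 (control) and 0.20 (HOPE), m_f = 0.30, m_n = 0.** The true difference is 0.20 × 0.30 = +0.060.

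| f | r | Measured difference |
|---|---|---|
| 0.15 | 0.30 | 0.20 × (0.30 − 0.045) = +0.051 |
| 0.25 | 0.30 | 0.20 × (0.30 − 0.075) = +0.045 |
| 0.50 | 0.30 | 0.20 × (0.30 − 0.15) = +0.030 |
| 0.50 | 0.60 | 0.20 × (0.30 − 0.30) = 0.000 |
| 0.80 | 0.40 | 0.20 × (0.30 − 0.32) = −0.004 |
| 0.80 | 0.60 | 0.20 × (0.30 − 0.48) = −0.036 |

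**Chance baseline.** Assume SDs of 0.15 (functioning) and 0.08 (failing). The per-patient variance is (1 − p)·0.15² + p·0.08² + p(1 − p)·0.30², which is 0.0337 for HOPE and 0.0377 for control. The standard error is √(0.0337/15 + 0.0377/30) = 0.059. A true difference of 0.060 is then about one standard error, and about 15% of such trials show the wrong sign with no dialysis effect at all. In simulation (40,000 trials of 15 versus 30 per row) the wrong-sign share is 19% and 21% in the first two rows of the table and runs from 28% to 72% in the last four. These shares must be read against the 15%.

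**Day 2 against day 5.** If every DGF patient is dialysed in the window (f = 1), reversal needs r > (m_f − m_n)/(1 − m_n).

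- Day 2, m_n = −0.10: r > 0.27 for m_f = 0.20, and r > 0.45 for m_f = 0.40.
- Day 5, m_n = −0.10, m_f = 0.60: r > 0.64. At r = 0.40 a true +0.140 becomes +0.052, so 37% is kept.

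Over a grid of assumed values (r 0.2–0.5; f 0.25–1; day 2: m_f 0.2–0.4, m_n −0.2 to 0; day 5: m_f 0.4–0.7, m_n −0.2 to 0.1):

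| Ratio | Settings | Reversed | Under 10% kept | Attenuated |
|---|---|---|---|---|
| Day 2 | 144 | 24 | 9 | 111 |
| Day 5 | 256 | 6 | 6 | 244 |

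These are counts of settings, not probabilities.

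**Opposite direction.** Dialysis before the day-1 sample lowers the day-2 denominator. With baseline creatinine 1 and a later rise of 0.10, the undialysed ratio is −0.10. After 30% removal it is −0.10/0.70 = −0.14, and after 40% removal −0.10/0.60 = −0.17. That failing graft scores worse, not better.

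**The case against.** The strongest reply is that the article is silent, not wrong. It is a condensed text, handling of values after dialysis is a derivation rule, and the full protocol or analysis plan may hold one. A reader might infer that the trial will compute the ratios in dialysed patients regardless; no sentence says so. What remains is that both ratios are printed as complete formulas beside a primary endpoint of dialysis. Followed as written, they score a dialysis-driven fall as graft function. That is a weakness in the definition and not only an omitted detail.

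A reader might also infer that HOPE's benefit will be cancelled or reversed. The documents do not support this: they give no DGF rate and no dialysis timing, attenuation is the usual result over the assumed ranges, and the size depends heavily on how many DGF patients are dialysed between two samples one day apart. Nor can one say that day 5 is affected at least as much; it is less prone to reversal.

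Extending the point to the laboratory time courses goes too far. The article says "Blood parameters of kidney function (ie, creatinine, urea, estimated glomerular filtration rate [eGFR]) will be monitored" and "Two-way analysis of variance will be used for the time-course analysis of laboratory parameters", but not that first-week values will be read as graft function without regard to dialysis.

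It is also fair that these are secondary endpoints in a small pilot, that DGF and its duration are reported alongside, and that the lowest-rank rule is one of several options. Exclusion or the last value before dialysis are others. These arguments limit the stakes; they do not make the printed formula a measure of graft function in a dialysed patient.

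**Conclusion.** The point holds as a defect in the definition of secondary endpoints. The two ratios, and functional DGF with them, do not say how dialysed patients are treated, and the formulas as printed mix removal by dialysis with graft function.

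If HOPE lowers DGF, the likeliest effect is dilution. On day 2 the assumed true +6.0 points becomes about +5.1 to +4.5 with light contamination and +3.0 to −3.6 with heavy contamination. Cancellation or reversal is therefore possible on day 2 and less likely on day 5, and dialysis before the day-1 sample works the other way on the day-2 ratio. All of these sizes rest on assumed DGF rates, ratios, removal fractions and timing. The primary endpoint is not affected. The change should be made, but it does not threaten the trial's main result.

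**What to change.** Add to the endpoint definition that a patient dialysed, or with graft loss or death, before the day-2 or day-5 sample takes the lowest rank for that ratio, and that the groups are compared with a rank test. Apply the rule identically to the historical controls. Report the ratio in undialysed patients as description or as a sensitivity analysis. For functional DGF, state that a patient on dialysis cannot be classed as free of it because of a dialysis-induced creatinine fall. If the full protocol or analysis plan already holds such a rule, citing it is enough.

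The cost is a few sentences and a few lines of code. Dialysis occurrence and the date of the last dialysis are already needed for the primary endpoint and for DGF duration; the rule also needs to know whether any dialysis preceded each sample. Enrolment was ongoing when the article was written, and the team is unblinded with historical controls, so the rule is best fixed before the data are examined. The downside is that the ratio becomes a rank comparison and partly overlaps with the primary endpoint.
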